# 3. STUDY DESIGN AND MEASUREMENT INSTRUMENTS

## 3.1 STUDY SUMMARY

We will include a total of **168 participants** in the current investigation, as outlined above.

This study will require five visits, which can be seen in the study schematic timeline, below. All visits and data collection will be conducted within the Ivor Wynne Centre at McMaster University.

## 3.2 DETAILS OF INITIAL STUDY DOCUMENTATION

Prior to the baseline study visit, all subjects will complete the following surveys / documents / tests to confirm their eligibility and suitability to participate in this investigation:

1. Standard medical questionnaire
2. CSEP Get Active Questionnaire and CSEP Get Active Reference Document
3. Global Physical Activity Questionnaire (GPAQ)
4. Seven-day food log
5. Informed consent form
6. Tissue consent form

All information acquired from phone calls or emails sent to interested participants prior to completing the documents above will be kept strictly confidential. Participants will be encouraged to contact any of the investigators if they have any questions or concerns about the study. A copy of all signed consent forms will also be added to each participants data file.

## 3.3 DETAILS OF STUDY VISITS

Participants will not be permitted to consume alcohol or caffeine for 24 hours prior to each study visit. All participants will be instructed to abstain from participating in sports or conducting exercise of any kind for 24 hours prior to each visit. Exceptions may be made if the individual cycles to work, but this must be discussed with investigators.

Participants will undergo the following assessments. Study visits that include the methods detailed below are specified for each evaluation and can be seen on the study timeline and schematic above (Section 3.1 Study Summary).

**HEALTH QUESTIONNAIRE**

Participants will complete the following health questionnaires. Please find these questionnaires attached to the online interface of this ethics document submission.

- DASS-21 is a 21-item self-report scale designed to measure negative emotional states of depression, anxiety, and stress. The essential function of this established questionnaire is to assess severity of the core symptoms of depression, anxiety, and stress as part of the broader task of clinical assessment.^31–33^
- ONLY PARTICIPANTS WITH T1D: The DIDP (DAWN Impact of Diabetes Profile) is a six question, single-factor survey that has been shown to reliably measure the perceived impact of diabetes on quality of life.^34, 35, 44^

**BODY COMPOSITION AND SYSTEMIC EVALUATION**

- DEXA scan will be conducted to assess body composition, including fat, bone, and muscle mass. This procedure takes approximately seven minutes, during which the participant will lay still while a sensor passes over their body. Anthropometric measurements of height and weight will be recorded, and body mass will be calculated using the equation BMI = weight/(height)^2^. These metrics are required to perform the DEXA scan.
- Blood sampling: A small needle will be inserted into a forearm vein and a blood sample will be drawn (approximately 20 mL). After the blood sample has been taken, pressure will be placed on the site to minimize bleeding.

Blood is being sampled for analysis of primary measures (including glucose, insulin, free fatty acids, cholesterol, triglycerides, HDL, LDL, HbA1c, lactate) and secondary measures (including serum creatine kinase, creatinine, urea, uric acid, potassium, PAI-1, and tryptophan metabolites (kynurenines)).

**MACROVASCULAR MEASURES**

- Blood pressure will be measured in triplicate with at least one minute rest between measurements using an automated oscillometric device. These measurements will be conducted while the participant is seated and following a ten-minute resting period.
- Arterial stiffness will be measured using pulse wave velocity (PWV). The time it takes a pulse to travel between two superficial arterial regions of interest (carotid-femoral and femoral-foot) is accomplished using applanation tonometry and is an indicator of central and peripheral arterial stiffness. Two applanation tonometers (SPT-301, Millar Instruments) will be placed superficially on the outlined regions of interest for 20 heart cycles to calculate central and peripheral arterial stiffness using the formula: PWV = distance / transit time. This assessment will be performed at rest and 1-, 10-, and 20-minutes following the test of aerobic fitness.
- Carotid intima-media thickness (cIMT) is the measure of the thickness of the common carotid artery walls and can be indicative of arterial plaque burden. B mode ultrasound will be used to capture images of the common carotid artery which will later be analyzed using semi-automated edge tracking software (Arterial Measurement Systems, AMS).
- Carotid distensibility (CD) is a measure of carotid artery elasticity or the rigidity of the vessel wall. Increased or large compliance values correspond to decreased or diminished arterial stiffness. Arterial compliance reflects the ability of an artery to expand and recoil with cardiac pulsation and relaxation. Decreased central arterial compliance has been identified as an independent risk factor for future cardiovascular disease. This assessment involves the simultaneous measurement of B mode ultrasound (Vivid q, GE Medical Systems) of the right carotid artery and applanation tonometry (SPT-301, Millar Instruments) of the left carotid artery for 10 heart cycles.
- Endothelial-dependent vasodilatory function will be assessed using brachial artery flow mediated dilation (FMD).^30^ FMD represents the dilatory capacity of an artery in response to a rapid increase in shear stress. It involves the placement of a blood pressure cuff around the forearm distal to the elbow. The cuff will be inflated above systolic blood pressure to ~200 mmHg (to cease arm blood flow) and held at this pressure for five minutes. Continual measures of brachial artery diameter and blood flow velocity will be obtained using Doppler ultrasound (Vivid q, GE Medical Systems). A 12MHz probe will be placed on the upper arm (below the biceps) and moved until the best signal is found. Images of brachial artery diameter and blood flow velocity will be taken at rest (before cuff inflation), prior to cuff deflation (end of five-minute ischemic period) and following cuff deflation for three minutes. FMD will be calculated using this formula: FMD% = ((peak diameter - baseline diameter) / baseline diameter) × 100%. These measurements can be used to quantify endothelial-dependent function and are also approved under the HiREB ethics protocol #8000.

**STRENGTH AND AEROBIC FITNESS TESTING**

- Muscle strength testing: Quadricep maximal isometric strength (maximal voluntary contraction; MVC) will be measured using an isometric dynamometer (Biodex). The protocol will consist of three five-second periods during which participants will be encouraged to maximally push against the padded lever strapped to their leg, with 30 second breaks between each repetition. The lever will be set to a knee joint angle of 90 degrees. Hand grip strength will also be tested using a hand grip dynamometer connected to a commercially available data acquisition unit (Powerlab). Bilaterally, participants will perform two MVCs on the handgrip dynamometer, and if the two measurements differ by 5% on the same hand, a third will be performed.
- Aerobic fitness testing: Depending on the success of the CSEP Get Active Questionnaire, a PWC130 or VO_2_Peak stationary bike test (Lode, Excalibur Sport) will be conducted to assess whole body aerobic fitness and exercise capacity. For individuals that answer “Yes” to any questions of the CSEP Get Active Questionnaire, and successfully complete the CSEP reference document, a PWC130 test will be performed: participants will complete two consecutive six-minute rides on a stationary bike. The resistance during these rides will have been selected to produce a heart rate of approximately 100-110 beats per minute in the first ride, and approximately 130-140 beats per minute in the second ride. A tiered system (i.e., PWC140, PWC150) will be used if required. For individuals that answer “No” to all of the CSEP Get Active Questionnaire, a VO_2_Peak test will be performed: participants will complete a cycling program with an incremental increase in resistance until exhaustion. The warm-up period will consist of two minutes at 50 Watts, followed by an incremental increase of one Watt each two-seconds. Successful achievement of VO_2_Peak (ml/kg/min) is obtained, and testing will stop, when any of the following are met: participant heart rate reaches their predicted maximum, respiratory exchange ratio exceeds 1.1, or when volitional exhaustion is reached.

**INTRAMUSCULAR MEASURES**

- Motor neuron evaluation: Non-invasive high-density surface electromyography (EMG; Sessantaquattro 64-channel EMG) will be used to determine changes in the neural control of muscle force production. Namely, motor unit properties such as recruitment threshold, discharge rate, and conduction velocity will be evaluated to identify possible alterations in the neural strategies regulating force production.

To begin, the skin over the quadricep will be shaved and cleansed. EMG signals will be initially recorded during a brief voluntary contraction during which a non-adhesive dry electrode will be moved over the skin to detect the location of the innervation zone and confirm muscle fiber orientation/direction. Surface EMG signals of the vastus lateralis will then be recorded with an appropriately positioned two-dimensional adhesive electrode grid whose cavities will be filled with conductive paste once affixed to the skin. A strap electrode will be dampened with water and positioned on the medial malleolus of the right leg to be used as a ground electrode. The EMG signals will be recorded in a mono-polar mode and converted to digital data through a multi-channel amplifier for evaluation and analysis.

- Microvascular function and perfusion will be evaluated within the quadricep (vastus lateralis) using the Contrast Enhanced UltraSound (CEUS) method.

CEUS uses gas-filled lipid microspheres with thin permeable shells that are 1-3µm in size. Once the microspheres are released into systemic circulation (via intravenous infusion through a forearm vein), they act as acoustic reflectors to enhance the contrast in collected ultrasound images. The microspheres are smaller than red blood cells, which allows them passage through the microcirculation, but prevents them from diffusing through vessel walls. Their echogenic properties allow the quantification of the level of contrast within a tissue over time which indicates the overall perfusion capacity.^39^ This technique records the contrast-enhanced acoustic time-intensity curve at low mechanical index (MI) (MI = .8) during steady state intravenous microbubble infusion. Briefly, once steady state is achieved, a high MI “flash” (MI = 1.32) is implemented to destroy microbubbles in the region of interest, where microbubble replenishment curves are subsequently recorded using curve-fitting techniques. High MI “flashes” and subsequent low MI recordings will be performed for the assessment of microvascular blood flow and reactivity at rest and following unilateral isotonic knee extensions at 50% 1-RM, respectively.^48,49^ Sulfur hexafluoride-containing lipid microspheres (SonoVue; Bracco, Milan, Italy) are activated by a vial mixer (Vialmix, Lantheus) at 75Hz for 45 seconds, after which the activated microbubbles are prepared for intravenous infusion.^42^ Preparation of activated microbubbles is carried out by an experienced operator, strictly following the instructions provided by SonoVue. Infusion (2ml/min for one minute, then 1ml/min thereafter) and venous catheterization (antecubital vein) will be performed by a trained operator.

Microbubble appearance will be assessed within the quadricep muscles, and slope of bolus-muscle-perfusion, wash-in time, maximum acoustic intensity, and integral of peak intensity will be calculated from both legs to evaluate microvascular function. These measurements are also approved under the HiREB ethics protocol #8000.

- The resting muscle biopsy procedure takes approximately 20 minutes and involves the removal of a small piece of muscle. [name], supervised by [name], will clean an area on the thigh and inject a small amount of local lidocaine anesthetic. She will then make a small incision (~4-5mm) in the skin into which the biopsy needle will be inserted. A small piece of muscle (~100 mg) will be removed by the biopsy needle. The incision will then be stitched closed and wrapped in a tensor bandage.

Muscle is being sampled for: mitochondrial bioenergetic measures, including carbohydrate and fat oxidation, as well as reactive oxygen species measures; histological and immunoblotting / fluorescent measures; electron microscopy; transcriptomic analysis on a select number of study participants.

**CONTINUOUS HEART RATE AND ACTIVITY MONITORING**

**Continuous throughout all 18 weeks of study**

- ALL participants will be provided with a Garmin Venu Sq watch following confirmation of eligibility to participate in this investigation. ALL participants will be instructed to wear this watch during the day and night for the entire duration of this study.
- On-the-wrist health and wellness monitoring will provide all participants with an overview of the following metrics, whose data will also be collected for the duration of this study:
  - Heart rate
  - Blood oxygen saturation during the day and during sleep
  - Physical activity intensity and duration
  - Hours and quality of sleep
  - Caloric expenditure
  - Respiration rate

**CONTINUOUS GLUCOSE MONITORING – ONLY PARTICIPANTS WITH T1D**

**Continuous throughout all 18 weeks of study**

- Individuals with T1D will also have their continuous glucose monitoring (CGM) device connected for time-in-target measures and evaluation for the entire duration of this study. If participants with T1D do not already use a CGM device, this device will be provided for their use for the entirety of their study participation.

## 3.4 DETAILS OF EXERCISE TRAINING

As detailed in the study timeline (section 3.1, above), individuals will participate in two blocks of exercise training – the first (exercise training in the study timeline) being twelve weeks in duration, and the second (exercise re-training in the study timeline) being four weeks in duration.

To model the current Diabetes Canada exercise guidelines^45^ as well as the current exercise recommendations of the Public Health Agency of Canada via the Canadian Society for Exercise Physiology,^46^ the following exercise guidelines will be provided to study participants.

- Partake in at least 150 minutes of moderate-to-vigorous-intensity aerobic exercise each week**.** Using your Garmin watch to monitor your heart rate during activity, activity minutes will be counted if they are WITHIN or ABOVE heart rate “Zone 3”, also called the “Aerobic” heart rate zone. You enter this zone when your heart rate (heart beats per minute) reaches 64% of your maximum calculated heart rate. Bouts of exercise will count toward your aerobic activity minutes if your heart rate moves into this “Aerobic” heart rate zone for a minimum of 10 consecutive minutes.
- Partake in resistance exercise two to three times per week. While this exercise does not require you to be in any specific heart rate zone, activity should continue for a minimum of ten consecutive minutes.
- Have no more than two consecutive rest days without exercise.

In addition to these guidelines, a suggested exercise calendar and home exercise video guide will be provided to participants to ensure ease of exercise participation and a consistent regime across all study subjects. Briefly, scheduled aerobic training (including high intensity interval training and brisk walks), and resistance training will be undertaken up to five days per week following an at-home exercise regime.

Participants will be educated in all exercises to ensure safety and competency. A lead-in phase, which will occur during weeks one and two of the exercise training period, replaces several structured exercise days with brisk walks. This will be utilized to introduce exercise and improve retention. The full exercise regime will commence from week three onwards. Participants with T1D will be directed to monitor their CGM to facilitate safety and educate them on glucose responses to exercise.

## 3.5 DETAILS OF DETRAINING PERIOD

Upon completion of the twelve-week exercise training period, all study participants will undergo a seven-day detraining period consisting of unilateral (single-leg) knee immobilization using a hinged knee-joint immobilization brace. While on the study participant, this brace will be locked at 60° of knee flexion. This position will ensure the foot is off the ground to prevent normal weight-bearing and will also allow knee extensors to stay relaxed.^47-50^ For ambulation, and to ensure no weight-bearing on the immobilized leg, participants will be provided with axillary crutches. Crutches will be adjusted according to the height of the participant, and training on the proper use of crutches, including navigation of stairs, doors, and other community obstacles, will be provided.

Participants will be instructed only to remove the knee brace in bed, prior to sleep. During bathing, participants will be instructed not to remove the brace, but to keep it dry by covering it with a large plastic bag provided by the research team. Participants will also be given a stocking to wear underneath the brace, which will be measured to extend from the proximal thigh to the ankle. The stocking is intended to mitigate discomfort and minimize the risk of skin irritation from the brace. Like the immobilization brace, this will be worn at all times and only removed during sleep.

In accordance with previous knee joint immobilization studies, participants will perform twice daily (morning and evening) range of motion movements of the ankle and knee to minimize the risk of vascular or muscular complications due to immobilization.^50-52^ Movements will be performed while lying in bed, and consist of knee flexion, ankle pumps, and leg lowers. A demonstration of these activities will be provided to participants prior to immobilization.

## 3.5 DETAILS OF RE-TRAINING PERIOD

As detailed in the study timeline (section 3.1, above), following completion of the detraining period, subjects will return to the exercise training plan for four weeks. Exercise training details are identical to those described in Section 3.4 – Details of Exercise Training, with the exception that a lead-in phase will not be used within the re-training period.

# 4. DATA ANALYSIS

Variables will be analyzed via a computerized statistical package (SPSS and GraphPad Prism). Differences in baseline measures between subjects with T1D and matched control participants, overall and stratified by young adults and older adults, as well as sex, will be assessed using t-test (if normal) or Mann-Whitney U test (otherwise) and chi-square or Fisher’s exact test for binary/categorical variables. Changes in baseline to post-training to post-detraining metrics for each group (male / female, young adult / older adult, T1D / non-T1D) will be examined graphically then using paired t-tests or Wilcoxon signed-rank tests, as appropriate. ANCOVA will be used to assess change score differences between groups and to assess sex differences using interaction terms. Despite subject matching, covariate analyses will be conducted to ensure that effects are adequately identified. P-values < 0.05 will be considered statistically significant. Additionally, due to its particular interest when studying disease populations, we will also calculate effect size using Hedges' g test to ensure that clinical relevance is considered along with traditional p-values.

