# 2. STUDY POPULATION, INCLUSION, AND EXCLUSION CRITERIA

## 2.1 STUDY POPULATION

Young (**18 to 30 years**) and older (**45 to 65 years**) adult females and males with and without confirmed T1D will be recruited to participate in this proposed investigation. All adults with T1D and without T1D will be matched for age, sex, and BMI at study onset. Subjects will also be matched for medication use, particularly statin and blood pressure medications. Participants must complete a standard medical questionnaire and physical activity readiness questionnaire (PARQ+) at study onset. Subjects should be sedentary or recreationally active, as defined by self-reported activity levels below the recommended 150-minute minimum of moderate-to-vigorous intensity physical activity per week, as recommended by Health Canada and Diabetes Canada.

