## 2.3 SAMPLE SIZE

We will include a total of **168 participants** in the current investigation – 84 participants with T1D, and 84 participants without T1D. Please see a breakdown of sample size by sex and age in the chart below. Groups are stratified in this way to ensure that appropriate comparisons between subjects with T1D and without T1D, overall AND stratified by young adult / older adult, as well as sex, may be made.

| Cohort | Age Group | Females | Males |
| --- | --- | --- | --- |
| T1D adults aged **18-30** (T1D duration <20 years) | Young adult | 18 | 18 |
| T1D adults aged **45-65** (T1D duration >30 years) | Older adult | 24 | 24 |
| Non-T1D adults aged **18-30** | Young adult | 18 | 18 |
| Non-T1D adults aged **45-65** | Older adult | 24 | 24 |

Power Calculation: Statistical analysis parameters were developed to allow sufficient power of Objective 1 primary outcome measures (the effect of T1D on skeletal muscle and microvascular health). Power calculations (2-sided test, power=0.8, alpha=0.05) were conducted using recently published and collected data from our lab. For Older adult subjects, mitochondrial density values (^26^; mu1 6.293, mu2 4.290, sigma 1.395) were used to reveal sufficient sample size for statistical power as n=17/sex/group. For Young adult subjects, Pax7-positive nuclei per 100-myofibers (indicative of skeletal muscle satellite cell content; preliminary data not shown herein; mu1 17.29, mu2 13.86, sigma 3.08) were used to reveal sufficient sample size for statistical power as n=13/sex/group. Both values were increased to a final sample size of older adult: n=24/sex/group and young adult: n=18/sex/group to provide a 40% excess to account for attrition and variability in initial aerobic fitness and responses to exercise training (exercise data was not available to derive appropriate power calculations). A full breakdown between groups can be seen in the table above. The longitudinal and paired nature of our methods further strengthens our statistical power for pre- and post- intervention analyses.

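### The overall Objective 1 comparison (84 v 84) is planned as a two-sample test that ignores the age-group and sex strata the design balances, so its standard error is too large whenever those strata predict the outcome

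*Protocol*

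**What the plan says.** Protocol section 2.1 fixes the matching: "All adults with T1D and without T1D will be matched for age, sex, and BMI at study onset". Medication use is matched as well. The section does not say whether matching is one-to-one or at group level.

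Section 2.3 sets "84 participants with T1D, and 84 participants without T1D", with equal T1D and non-T1D numbers in each age-by-sex cell: 18 young women, 18 young men, 24 older women and 24 older men per group. The stated purpose is: "Groups are stratified in this way to ensure that appropriate comparisons between subjects with T1D and without T1D, overall AND stratified" by age group and sex. The study is sized on Objective 1, per sex and per age group.

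Section 4 gives the tests. Baseline differences on continuous measures, "overall and stratified by young adults and older adults, as well as sex", "will be assessed using t-test (if normal) or Mann-Whitney U test (otherwise"). Paired tests are named only for changes over time, which "will be examined graphically then using paired t-tests or Wilcoxon signed-rank tests, as appropriate". Interaction terms are named once, for sex, in the ANCOVA sentence that deals with change scores. One further sentence reads: "Despite subject matching, covariate analyses will be conducted to ensure that effects are adequately identified". It names no covariates and no model, and does not say how the result ranks against the t-test.

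**The concern.** Because the design fixes the same age-by-sex mix in both groups, differences between young and older adults and between women and men cancel from the group difference. They do not cancel from the standard error that a two-sample t-test calculates. That test puts all the spread within each group, including the spread between strata, into its error term. If age group or sex predicts the outcome, the reported standard error is too large, the confidence interval too wide and the p-value too high. A rank test on the pooled groups has the same weakness.

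The overall comparison is affected, and so is each one-factor subgroup: the young-adult comparison still pools women with men, and the comparison in women still pools young with older. At stake are moderate T1D differences on outcomes that vary strongly with age or sex.

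A second gap concerns effect modification. Age group is a design factor, but no test of T1D by age group is named. Separate tests in young and older adults invite the comparison of two p-values, which does not test whether the T1D difference varies with age.

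**Working it through.** **The plan's own figures.** Section 2.3 uses two-sided alpha 0.05 and power 0.80. With n per group = 2(1.960 + 0.842)²/d²:

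- Young: d = (17.29 − 13.86)/3.08 = 1.114, so n = 12.7, rounded up to 13. This matches the stated 13.
- Older: d = (6.293 − 4.290)/1.395 = 1.436, so n = 7.6, rounded up to 8. The stated 17 does not follow from these inputs. That is a separate matter and does not affect this point.

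Both calculations are for two-sample tests within one age-by-sex cell. Age group and sex are constant there, so the inflation examined below is zero.

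**Inputs for the overall comparison.** From the protocol: 84 per group, cells of 18, 18, 24 and 24 in each group, two-sided alpha 0.05. Assumed, because the protocol gives neither: R², the share of within-group variance explained by the strata, from 0 to 0.6; and a true difference of 0.4 within-stratum SD.

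**Formulas.** With the within-stratum SD set to 1:

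- True SE of the difference under balance: √(2/84) = 0.154.
- SE that the two-sample test uses: 0.154/√(1 − R²). It is too large by the factor k = 1/√(1 − R²).
- Actual type I error: 2[1 − Φ(1.96k)].
- Power: Φ(0.4/0.154 − 1.96k) = Φ(2.592 − 1.96k).

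Simulation of the 18/18/24/24 cells, using the t distribution, agrees closely with the formulas:

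| Assumed R² | SE too large by | Type I error: formula / simulated | Power, two-sample test: formula / simulated | Power with strata in the model (simulated) |
|---|---|---|---|---|
| 0 | 0% | 5.0% / about 5% | 74% / about 73% | about 73% |
| 0.1 | 5% | 3.9% / about 3.8% | 70% / about 69% | about 73% |
| 0.2 | 12% | 2.8% / about 2.8% | 66% / about 65% | about 73% |
| 0.4 | 29% | 1.1% / about 1.2% | 52% / about 52% | about 73% |
| 0.6 | 58% | 0.2% / about 0.2% | 31% / about 30% | about 73% |

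The row for R² = 0 shows that stratifying costs no measurable power when the strata explain nothing.

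**At the protocol's own effects.** Taking 1.114 as the within-stratum difference, 1.114/0.154 = 7.2. Even at R² = 0.6 the threshold is only 1.96 × 1.58 = 3.1, so power exceeds 99.9%. The same holds for 1.436.

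**Separate significance by age group.** The young comparison has 36 per group (18 + 18) and the older one 48 (24 + 24). The difference detectable with 80% power, 2.80 × √(2/n), is 0.66 SD and 0.57 SD respectively. A T1D difference of the same true size is therefore more likely to be significant in older adults.

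**The case against.** The strongest reply has five parts.

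- **The plan does stratify.** A reader might infer that the whole of Objective 1 is tested without regard to strata. The protocol does not support that: the sentence naming the tests also calls for comparisons by age group and by sex. The point reaches the overall test and, for the other factor, the one-factor subgroups.
- **Adjustment is planned.** A reader might infer that it is absent. It is not; it is left unspecified, and the protocol ranks neither analysis above the other. Detail of this kind can be left to a statistical analysis plan. What remains is that the protocol names a particular, less efficient test for a balanced design and gives no rule for which result governs if the two differ.
- **An unpaired test may be correct.** A reader might infer that matched data require a paired test. That follows only if matching is one-to-one, which section 2.1 does not say. Pairing can even cost power: for 18 young adults per group at d = 1.114, the unpaired test has 90.1% power and the paired test 88.2% if the within-pair correlation is zero.
- **The powered comparisons are untouched.** This stands. The study is sized within age-by-sex cells, and at the protocol's effect sizes the loss in the overall test is negligible. But those effects belong to mitochondrial density and satellite cell content. Objective 1 also covers strength, aerobic fitness, body composition and vascular measures, for which no effect size is given.
- **The error is in the safe direction.** This also stands. The estimate is unbiased and false positives do not increase.

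**Conclusion.** The point holds as one of efficiency and clarity. The named test for the overall 84 v 84 baseline comparison does not use the balance that sections 2.1 and 2.3 build in. Its standard error is too large by 1/√(1 − R²) whenever age group or sex predicts the outcome. The documents do not fix the size of the loss: it runs from nothing at R² = 0 to a standard error 58% too large at R² = 0.6. The power figures also rest on the assumed 0.4 SD difference.

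A reader might go further and conclude that Objective 1 is underpowered, biased or invalid. The protocol does not support any of these. Separately, with interaction terms named only for sex, the plan as written has no test of whether the T1D difference varies by age group. Nothing in the protocol says that differing p-values would be read as an age effect, but nothing else is offered to answer the question.

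**What to change.** In section 4:

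- State whether matching is one-to-one or at group level.
- Make the main Objective 1 analysis of each continuous outcome one linear model with T1D status, age group, sex, age group × sex and BMI, using a transformed or rank-based outcome if it is skewed. Add a pair term only if matching is one-to-one.
- Test T1D × age group and T1D × sex in that model, and report stratum differences as contrasts from it rather than from separate tests.
- Keep the unadjusted t-test or Mann-Whitney test as supportive.

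The cost is one paragraph. Age group, sex and BMI are already collected, and no change to recruitment or sample size is needed.
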